**Methods:**

This is a randomized, cross-over clinical trial. Forty men aged 18 to 30 years, healthy and physically active according to the International Physical Activity Questionnaire will participate in the study. Participants will be randomized into groups, which will perform the five interventions of the study at randomized moments, one intervention per session: Intervention 1: control; Intervention 2: participants will receive the massage protocol; Intervention 3: performance of the stress protocol; Intervention 4: participants will perform the stress protocol and immediately after receive the massage; Intervention 5: participants will perform the stress protocol and 1 h after conclusion of the protocol will receive the massage. The sessions will occur with an interval of 1 week between them and, due to the technique used, blinding participants and therapists is not possible. The primary outcome measure is HRV that will be measured 2 h after the conclusion of each intervention, and secondary outcome measures, which include heart rate, respiratory rate, blood pressure, oxygen saturation, and individual touch perception, will be measured at specific moments in the course of each intervention.

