### Randomization

Participants who meet the eligibility criteria and sign the consent form will be randomized, using simple randomization, for logistic reasons into five groups and the groups will be randomized into the different interventions of the study to determine the order of accomplishment. In order to guarantee the hidden allocation of the participants in the groups and the randomization of the study interventions, a researcher not involved in the recruitment will be responsible for this procedure using electronic software (Microsoft Office Excel). This researcher will be instructed not to previously inform the participants or other researchers about the procedures that will be performed in each session. The following figure presents the schematization of the aforementioned randomization processes (Fig. 2).

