### Sample size

As described above the primary outcome will be the HRV. The sample size calculation was carried out based on the study of Arroyo-Morales et al. [15] in which the SDNN Index of the HRV was selected, since it is an index that expresses the behavior of the ANS in a global way. To establish the sample size, a mean effect of 26.9 and standard deviation of 38.8 were chosen. The level of significance for the sample size is 5%, the power test is 80%, two-tailed test, and 10% of the total value of *n* is added to statistically supply the analyses in the case of withdrawals during data collection. The value obtained for the sample size was 33 participants, adding the 10% gave a sample of 36 volunteers. However, there are other indices besides the SDNN Index within the HRV, and this situation generates an environment where the sample size could be underestimated. In the same sense, due to the new proposal presented by the study, there are no trials in the literature that have the same proposal dynamics, and thus, for safety we will add four volunteers to ensure the statistical analysis of all HRV indices, thus totaling a sample of 40 participants.

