### Statistical analysis

For analysis of the data of the population profile, the descriptive statistical method will be used and the results presented as values of means, standard deviations, median, minimum and maximum numbers, and confidence interval. The normality of the data will be evaluated through the Shapiro-Wilk test.

The comparisons of cardiorespiratory parameters and HRV indices between interventions (I1, I2, I3, I4, and I5) and moments (rest (R1) vs recovery moments (R2–R12)), the data are analyzed from the prism of the covariance analysis (ANCOVA), which will be adjusted for the baseline value of the evaluated variable and generated estimated means after such adjustment (extracting the variance explained by the confounding variables). The Levene test will be used to prove the homogeneity of the variances at the created moments, and the Bonferroni post hoc test will be used for comparison. To guarantee homogeneity of data the variable can will be transformed into logarithm.

For analysis of the moments (rest vs recovery moments), repeated measures ANOVA with the Tukey post test for parametric distribution or Friedman test with Dunnett’s post test for non-parametric distribution will be used and the analysis of the different groups will be performed by means of one-way ANOVA with the Tukey post test or the Kruskal-Wallis test with Dunnett’s post test.

The level of significance will be *p* < 0.05 for all tests. The SPSS statistical program (version 13.0) (SPSS Inc., Chicago, IL, USA) will be used for the analyses. Data integrity will be monitored by regularly scrutinizing data files for omissions and errors. Participants will be given an anonymous study ID to protect confidentiality, and only study investigators will have access to the final trial data set.

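### If the 'different groups' are the five interventions, one-way ANOVA and Kruskal-Wallis treat repeated measurements of the same 40 men as independent samples; if they are the order groups, the test compares no interventions

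*Protocol article*

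**What the plan says.** The Abstract (Methods) describes a cross-over in which participants are put into groups, "which will perform the five interventions of the study at randomized moments, one intervention per session". Each man therefore supplies data under all five conditions, and the Sample size section ends at 40 men.

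The Statistical analysis section describes three analyses of the outcomes:

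- An ANCOVA adjusted for the baseline of the variable, with Bonferroni post hoc tests. It covers "The comparisons of cardiorespiratory parameters and HRV indices between interventions (I1, I2, I3, I4, and I5") and the moments.
- For the moments only, repeated measures ANOVA, or Friedman if the data are not normal.
- Then, in the same sentence as the moments, "the analysis of the different groups will be performed by means of one-way ANOVA with the Tukey post test or the Kruskal-Wallis test".

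The Randomization section uses 'groups' in another sense. Men are randomised "for logistic reasons into five groups and the groups will be randomized into the different interventions of the study to determine the order of accomplishment". There the groups are sets of men who share an order of sessions.

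**The concern.** One-way ANOVA with Tukey and Kruskal-Wallis assume that the samples compared come from different people. The plan reserves its within-person tests for the moments and gives the 'groups' the independent-samples tests. If the groups are I1 to I5, the five samples are the same men. Part of the spread in HRV is then stable difference between men. A cross-over removes that part from the comparison of conditions, but a one-way analysis leaves it in the error term.

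What is at stake is a missed difference, not a false one. The Study interventions section names the comparison of massage immediately after stress with massage one hour later (I4 against I5). That is a pairwise contrast, and pairwise contrasts and their intervals are where the loss shows most. A real timing effect could be reported as no difference.

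**Working it through.** **Inputs.** From the Sample size section: "a mean effect of 26.9 and standard deviation of 38.8 were chosen", two-sided 5% level, 80% power, 40 men. From the design: five conditions per man. Assumed: a common within-man correlation ρ between sessions, and 38.8 as the SD between men under one condition. The protocol gives no ρ and does not say which SD 38.8 is.

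**The plan's own figure.** For two independent groups, n = 2 × [38.8 × (1.960 + 0.842) / 26.9]² = 32.66, rounded up to 33 per group. This reproduces the stated 33. Then 33 × 1.1 = 36.3, stated as 36, and four more give 40. A paired formula with 38.8 as the SD of differences gives 16.3, so 17 men (19 with the exact paired t), and does not reproduce 33. The sample size therefore also follows an independent-samples calculation.

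**Interval width for one pair of conditions, n = 40.**

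- Unpaired SE = 38.8 × √(2/40) = 8.68, whatever ρ is.
- Paired SE = 38.8 × √(2(1 − ρ)/40) = 8.68 × √(1 − ρ).
- Width ratio = 1/√(1 − ρ).

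| Assumed ρ | Unpaired SE | Paired SE | Ratio |
|---|---|---|---|
| 0 | 8.68 | 8.68 | 1.00 |
| 0.3 | 8.68 | 7.26 | 1.20 |
| 0.5 | 8.68 | 6.13 | 1.41 |
| 0.7 | 8.68 | 4.75 | 1.83 |

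**Power and test size.** Simulation of 40 men, five conditions, equal correlations, SD 38.8 and one value per session. One condition is shifted by 26.9 for the power columns and none for the size column. The one-way analysis uses the error mean square on 195 df. The within-man analysis removes the participant effect and uses 156 df.

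| Assumed ρ | Tukey power for one pair, one-way | Same, within man | True size of the nominal 5% one-way F test |
|---|---|---|---|
| 0 | about 63% | about 63% | about 5% |
| 0.3 | about 67% | about 83% | about 1% |
| 0.5 | about 69% | about 94% | about 0.15% |
| 0.7 | about 73% | nearly 100% | about 0% |

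The within-man F test keeps a size of about 5% throughout.

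**The other reading.** If 'groups' means the order groups, the samples do hold different men, about 40/5 = 8 per group if they are equal in size. But every group receives all five interventions, so a comparison between groups contrasts orders of sessions. It estimates no effect of massage or of its timing.

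**The case against.** Five things can be said for the plan.

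- **Vocabulary.** Elsewhere the protocol uses 'groups' for the order groups and 'interventions' for I1 to I5. On that usage the test is a valid independent-samples test. This stands as a possible reading, so the main point is conditional. It does not save the sentence, because comparing order groups answers no stated objective.
- **ANCOVA.** A reader might infer that the trial discards all the precision of its cross-over. The documents do not support that. The interventions are also compared by an ANCOVA adjusted for baseline, and R1 is recorded before the interventions, so that adjustment may remove part of the between-man variance. The ANCOVA names no participant term, which is a separate matter.
- **Power.** A reader might infer that the missing pairing alone takes pairwise power below 80%. It does not: Tukey over ten pairs gives about 63% even at ρ = 0. At the planned effect the overall one-way F test still has about 89% to 96% power for ρ from 0 to 0.8, and 33 was an independent-samples figure from the start.
- **Direction.** The error is conservative and does not inflate false positives.
- **Conflicting results.** A reader might infer that the report will carry two conflicting p-values. That is only a possibility. Which analysis ranks first is commonly settled in a fuller plan that is not shown, so the lack of a ranking here is no finding.

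**Conclusion.** The point holds in conditional form. If 'groups' means I1 to I5, the named tests are wrong for this design and lose precision whenever the within-man correlation is positive. If it means the order groups, the analysis serves no stated objective. The sentence needs to change either way.

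The size of the loss rests on an assumed correlation, on equal correlation between all sessions, and on 38.8 being the between-man SD. The part due to pairing is the gap between the two power columns: about 16, 25 and 27 percentage points at ρ = 0.3, 0.5 and 0.7, and none at ρ = 0. The claim covers the one-way ANOVA and Kruskal-Wallis analysis only, not the whole analysis plan.

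**What to change.** Delete the one-way ANOVA and Kruskal-Wallis comparison of interventions, and compare I1 to I5 within man in one of two ways:

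- a repeated-measures analysis of one value per session, either a single moment or a session summary; or
- a mixed model for all moments, with random effects for participant and for participant-by-session, and with intervention, moment, their interaction, session number and R1 as terms.

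As the rank alternative, use Friedman across the five interventions on one value per session. If a comparison of order groups was intended, say so and give its purpose.

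The participant-by-session effect matters. With only a participant effect over 11 recovery moments per session, variation shared within a session is treated as independent noise. In a no-effect simulation (40 men, five sessions, R1 as covariate, participant fitted as a fixed effect, participant variance assumed at 50% of the total), the nominal 5% intervention test rejected about 48%, 70% and 77% of the time when session-level variance was 10%, 20% and 30% of the total. That would replace a conservative error with a serious anti-conservative one.

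Cost: wording in the Statistical analysis section only. No new data are needed.

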However, in the study of Arroyo-Morales et al. [15] some gaps can be identified in the literature. Before the massage technique, the participants performed 15 min of active and passive recovery, the massage technique had five different modalities of tissue manipulation applied in regions that were not protagonists during the stress, with prolonged duration and applied only at one moment. These details in the design of the study may influence the responses found in the recovery of autonomic modulation of heart rate, especially considering practical applications. However, the main gap addressed by the present study protocol is related to the moment of application of massage as a recuperative technique. To study the optimal timing of the technique seems interesting since various sports modalities participate in several competitions throughout the day and, thus, it is necessary to understand the best moment of application of the recuperative technique to guarantee the best performance of the athletes.

The recovery of autonomic modulation of heart rate has been considered an important global marker of athlete recovery. Ihsan et al. [16] reported that the return of HRV values is a good indicator for exercise dynamics to be applied in training or in competitions. In addition, although massage is widely used as a recuperative technique, there are gaps in the literature regarding the effectiveness of massage in the autonomic modulation of heart rate and cardiorespiratory parameters; and especially in relation to the best moment of application. It is unclear whether performance of the massage technique has a beneficial effect on HRV both to anticipate its recovery and potentiate the effects of recovery depending on the moment of its application.

The present study is a randomized clinical trial aimed at investigating the effects of massage as a recuperative technique on the recovery of autonomic modulation of heart rate and cardiorespiratory parameters in physically active young people comparing two distinct scenarios: (1) immediately after stress in order to investigate if the technique anticipates the recovery of the ANS, and (2) immediately after the recovery moment of the ANS in order to investigate whether the technique potentiates the recovery of the ANS.

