### Procedures

#### Study interventions

The description of the interventions is as follows:*Intervention 1 (I1)*: the HRV behavior of the participant will be evaluated without exposure to any recovery technique or any type of stress. The follow-up period will be 2 h*Intervention 2 (I2)*: the HRV behavior of the participant will be evaluated before the application of the massage technique. Evaluations will be performed 2 h after massage application*Intervention 3 (I3)*: the HRV behavior of the participant will be evaluated before the implementation of the stress protocol. The autonomic modulation of heart rate will be evaluated 2 h after the end of the stress protocol*Intervention 4 (I4)*: the HRV behavior of the participant will be evaluated before the stress protocol, followed immediately by the massage technique, as well as 2 h after the completion of the massage in order to observe if HRV is anticipated*Intervention 5 (I5)*: the HRV behavior of the participant will be evaluated before the stress protocol, and the massage technique will be applied at the exact moment of ANS recovery, determined by the study of Almeida et al. [11] who used the same stress protocol, and posteriorly there will be follow up for 2 h in order to see if there is potentiation of HRV recovery

The first three interventions of the study (I1, I2, and I3) will be performed to establish the basal behavior of the study variables and/or before the two different stimuli (massage and stress), and for possible explanations and discussion of the study.

In Interventions 4 and 5, analysis of the effects of massage on post-exercise recovery, and the comparison of the effects of massage when performed immediately after stress or 1 h after stress, will be performed.

It is emphasized that at I5 the massage will be applied 60 min after the end of the stress protocol, as this was the exact time identified in the study by Almeida et al. [11] for the recovery of the internal control functions of the body after the same stress protocol as used in the present study.

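### The post hoc comparisons change with the normality result and do not match the plan's own questions: the rank branch as worded may leave out I4 vs I5, and Tukey covers 66 moment pairs where 11 are asked

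*Protocol article*

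**What the plan says.** All the analysis text is in the protocol article, Statistical analysis.

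- **Choice of branch.** "The normality of the data will be evaluated through the Shapiro-Wilk test". The later tests are then listed in parametric and non-parametric versions.
- **Moments (rest against recovery).** "repeated measures ANOVA with the Tukey post test for parametric distribution or Friedman test with Dunnett’s post test for non-parametric distribution".
- **Groups.** "one-way ANOVA with the Tukey post test or the Kruskal-Wallis test with Dunnett’s post test". No control or reference condition is named for Dunnett in either place.
- **A separate analysis, set out first.** A baseline-adjusted ANCOVA is given for "comparisons of cardiorespiratory parameters and HRV indices between interventions (I1, I2, I3, I4, and I5") and for rest (R1) against the recovery moments (R2 to R12). For this analysis, "the Bonferroni post hoc test will be used for comparison". Its remedy for unequal variances is a log scale: "To guarantee homogeneity of data the variable can will be transformed into logarithm". It carries no normality condition.
- **Significance.** All tests use p < 0.05. Neither between-intervention analysis is said to take precedence.

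On the question itself, the Background states that "the main gap addressed by the present study protocol is related to the moment of application of massage as a recuperative technique". Under Study interventions, for I4 and I5, "the comparison of the effects of massage when performed immediately after stress or 1 h after stress, will be performed". The Abstract calls only I1 the control.

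**The concern.** Tukey and Dunnett answer different questions. Tukey tests every pair; Dunnett tests each condition against a single control. Attaching one to the parametric branch and the other to the rank branch lets a preliminary normality test decide which contrasts are examined, not only how they are tested. Six HRV indices are analysed (rMSSD, SDNN, LF, HF, SD1, SD2), so the contrasts reported could differ from index to index.

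Between interventions, the contrast at risk in the rank branch is I4 vs I5, which the trial exists to make. Between moments the mismatch runs the other way. Comparison with rest is a many-to-one question, but the parametric branch pays for every pair of moments. If recovery is read as the first moment that no longer differs significantly from R1, the lost power makes HRV look recovered earlier than it is.

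**Working it through.** **0. The plan's own figure.** The plan gives no figure for the number of comparisons. Its sample size reproduces as a two-group calculation for one comparison at 5%: 2 × (1.96 + 0.8416)² × (38.8/26.9)² = 2 × 7.849 × 2.080 = 32.7, so 33. This point does not change it.

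**1. Intervention pairs.** There are five interventions. All pairs: 5 × 4 / 2 = 10. Many-to-one: 5 − 1 = 4. The contrasts on massage after exercise are I4–I5, I4–I3 and I5–I3. Which of them a literal Dunnett test keeps depends on the control:

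| Control | I4–I5 | I4–I3 | I5–I3 |
|---|---|---|---|
| I1 | no | no | no |
| I2 | no | no | no |
| I3 | no | yes | yes |
| I4 | yes | yes | no |
| I5 | yes | no | yes |

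I4 vs I5 is absent for three of the five possible controls, including I1. No choice keeps all three contrasts. Tukey keeps all three.

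**2. The ANCOVA.** Bonferroni over all 10 pairs tests each at 0.05 / 10 = 0.005 and includes I4–I5 whatever the Shapiro-Wilk result. The article does not list the pairs.

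**3. Moment pairs.** There are twelve moments, R1 to R12. All pairs: 12 × 11 / 2 = 66. Against R1: 11.

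**4. Cost of 66 instead of 11 in the parametric branch.** Assume 40 men with complete data and a standard repeated measures ANOVA within one intervention.
- Error df = (40 − 1) × (12 − 1) = 429.
- Tukey, k = 12: critical t = (studentized range quantile)/√2 = 3.286, or p < 0.0011 per comparison.
- Dunnett, 11 comparisons, by simulation: critical t = 2.757, or p < 0.0061 per comparison.
- Take a true difference from rest that a single unadjusted 5% test would detect with 80% power (non-centrality about 1.96 + 0.84 = 2.8). The non-central t gives power 0.315 under Tukey and 0.518 under Dunnett.

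**5. How often the rank branch might be reached.** The documents give no distribution. If an index were lognormal with log-SD 0.3, 0.5 or 0.8 (assumed), simulated Shapiro-Wilk tests at n = 40 reject in about 47%, 85% or 99% of data sets. This applies to raw-scale data only; after a log transformation such data would be normal.

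**The case against.** The strongest reply is that I4 vs I5 is never in danger. The ANCOVA covers I1 to I5, has no normality condition, and turns to logarithms rather than ranks. A reader might infer from the Dunnett wording that the plan cannot compare the two massage timings for a skewed index. The documents do not support that. What stands is narrower: two between-intervention analyses sit side by side at p < 0.05, and the text does not say which decides if they disagree or cover different pairs.

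Three further replies have weight.

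- **The group sentence may not concern I1 to I5.** Under Randomization and Design description, groups are the five randomised sets of participants and the conditions are called interventions. One-way ANOVA and Kruskal-Wallis are also tests for independent groups. On that reading the count of 10 against 4 does not apply to the massage contrasts. The text does not settle it.
- **Dunn's test may have been meant.** Dunnett's classical test is parametric, yet here it follows both rank tests with no control named. If Dunn's all-pairs test was intended, no intervention pair is lost and the error is one of naming.
- **The control could be I4 or I5.** Then I4 vs I5 is kept. Nothing in the article suggests this.

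On moments, Tukey controls the family-wise error and contains all 11 comparisons with R1. It would be wrong to call it invalid; it is only conservative. But this part survives every reading. With Dunnett taken literally, the two branches test 66 and 11 pairs. With Dunn's all-pairs test, both branches test 66 for a question that needs 11.

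**Conclusion.** The point holds as a defect in how the comparisons are fixed, not as the loss of the trial's main comparison.

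- **Between interventions.** If the groups are I1 to I5 and Dunnett is meant literally, the family falls from 10 pairs to 4 on a failed normality test, and I4 vs I5 goes untested in that branch unless I4 or I5 is the control. The ANCOVA can still test it but is not named as decisive. If Dunn's test was meant, the name needs correcting.
- **Between moments.** The parametric branch uses 66 pairs for an 11-comparison question. The critical t rises from 2.76 to 3.29, and power falls from 52% to 32% for the assumed effect. The power figures rest on the chosen non-centrality of 2.8, not on the protocol's 26.9 and 38.8, and on 40 complete participants. The counts rest on no assumption beyond the literal meaning of the test names.

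The independence assumption of one-way ANOVA and Kruskal-Wallis in a cross-over is a separate matter and is not relied on here.

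**What to change.** In Statistical analysis:

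1. State whether the group comparison concerns the interventions or the randomised groups.
2. Name one set of intervention comparisons, including I4 vs I5, and use it in both branches. The set I4–I5, I4–I3, I5–I3 would serve, as would all 10 pairs.
3. Replace or correct the Dunnett wording after Kruskal-Wallis so that it names a procedure for that same set.
4. State that the baseline-adjusted ANCOVA, on the log scale if needed, is the deciding between-intervention analysis and that the other is supportive.
5. For moments, compare each of R2 to R12 with R1 only, in both branches: 11 comparisons by Dunnett or Holm, or Holm-adjusted Wilcoxon signed-rank tests of the same 11 if non-parametric.

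The cost is a few sentences, with no new data and no change to the sample size. The downside is that pairs outside the named sets become descriptive.
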